A number of studies has shown that preventive interventions, particularly stepped-care ones, can lead to a reduction of up to 25% in the rate of depression in diseases such as diabetes [10]. Most of the research, however, has been focused on reducing depressive symptoms and disorders, and there is less directed at obtaining health benefits regarding the parameters of the associated medical illness [11, 12]. According to the literature, there are greater benefits to be had from intervening rather than not [10,11,]. Nevertheless, there is some controversy over whether specific and specialized interventions are better than more general ones such as health education regarding the associated chronic pathologies [13, 14]. As an example, the DIAMOS study reported that behavioral techniques led to both a decrease in depressive symptoms and a reduction in blood glucose levels [15].

With regard to psychoeducation, it has been demonstrated that it is an effective therapy in the treatment of depression in adults [16, 17] as it decreases depressive symptoms and risk of relapse/recurrence, and improves treatment compliance [17–19]. Adherence to psychoeducation interventions is high, according to some authors, with a reported attendance of 73–87% in all the group sessions [18, 20]. Moreover, such therapy could be carried out in primary care by community nurses with previous training [18, 20].

We present a study protocol of a randomized controlled trial aimed at evaluating the effectiveness of a psychoeducation group intervention carried out by primary care nurses in patients with depression and chronic physical illness (diabetes, COPD, asthma and/or ischemic cardiopathy). The main objective is to evaluate whether such an intervention improves the rate of remission and response of depression in these patients. Secondary ones include assessing the cost-effectiveness and feasibility of the intervention, its efficacy in improving control of the physical pathology, and its impact on health-related quality of life (HRQoL).

The primary hypothesis is that in patients with chronic physical disease pyschoeducation group therapy provided by primary care nurses can achieve a greater rate of remission and response of depression than habitual clinical practice.

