### Intervention

#### Description of the psychoeducation group intervention

In order to homogenize the interventions, the research group has developed a protocol of 12 weekly sessions lasting 90 min led by two primary care nurses. Each group is made up of 8–12 participants [26]. The sessions will be held on PHC premises which have the necessary space and equipment.

The objectives of the 12 sessions are depicted in Table 1. The program provides: 1) health education about chronic pathology and depressive symptoms; 2) information on the relationship between depressive symptoms and chronic pathology; 3) health education regarding: diet, physical exercise, sleep, pleasant activities, social skills, pharmacological treatment, and adherence to treatment; 4) breathing techniques; 5) problem solving, behavioral activation, and cognitive-behavioral perspective on depression; and 6) self-esteem and assertiveness [26].

**Table 1 Tab1:** Content of the psychoeducational group program

lSessions	Objectives
1	• First contact with the group • Identification of depressive symptoms • Information on chronic pathology versus chronicity • Information on the relationship between depressive symptoms and chronic pathology • Breathing techniques
2	• Behavioural Activation I: Concern and problems.
3	• Behavioural Activation II: Concern and problems.
4	• How to take care to advance I ➢ Healthy diet ➢ Motivation for change (resources and difficulties)
5	• How to take care to advance II ➢ Physical exercise ➢ Pleasant activities, social skills
6	• How to take care to advance III ➢ Sleep ➢ Therapeutic compliance
7	• Problem solving I
8	• Problem solving II
9	• Self-esteem and assertiveness
10	• Cognitive-behavioural perspective I
11	• Cognitive-behavioural perspective II
12	• Group farewell • Final evaluation

To enhance the active role of the patient, each session is accompanied with homework. The participants are free to continue under pharmacological treatment.

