#### Description of the control group

Members of the CG receive their usual treatment, that is to say, they can consult their family doctor/nurse as needed with no set pattern. The appointments last from 10 to 20 min and for both groups the healthcare professionals use their own criteria (usual clinical practice) regarding the chronic pathology and depressive symptoms.

The nurses receive prior training based on the intervention protocol [26] including the content of the 12 sessions. It consists of 20 h (10 theory and 10 practice) and is given by psychologists and nurses specialized in mental health.

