Sex, age, civil status, educational level (without studies / incomplete primary ones / completed primary ones / secondary ones / higher education), employment status (employed / housewife / unemployed / disabled / retired). Assigned PHC: rural (doctor’s surgery) / semi-urban (PHC with a population < 15,000 inhabitants) / urban (PHC with a population ≥ 15,000 inhabitants).

Primary outcomes*Clinical remission and/or response of depression* at short and long-term (one year follow-up) of the intervention following Riedel et al. [32]: clinical remission considered as a reduction in the rating < 13 of the BDI-II; response to the intervention as a decrease of at least 50% in the initial evaluation of depressive symptoms according to the BDI-II.

Secondary outcomes

*Improvement in the control of the chronic pathology* at 12 months follow-up:
Diabetes mellitus: controlled with glycosylated hemoglobin, HBA1C (%) [33, 34].COPD: lung function measured by post bronchodilator expiratory volume (FEV1). Dyspnea evaluated by the modified score of the Medical Research Council (mMRC), at 5 points [35, 36]Asthma: lung function measured by post bronchodilator expiratory volume (FEV1). Determination of peak expiratory flow (PEF) [37].Ischemic cardiopathy: measurement of levels of low-density lipoprotein cholesterol and blood pressure [38].
2.*Adherence to medication* is assessed by the *Morinsky-Green* test [39] and the comparison between containers collected in the pharmacy and those prescribed. It will be performed for all the prescribed medication for both groups.3.*Quality of life* as measured with the *EuroQol (EQ-5D-5 L)* questionnaire. (Original: EuroQol Group 1996. Spanish adaptation: Badia et al. 1999) [40, 41].4.*Utilization of healthcare services* during the study period. This includes: number of hospital admissions (emergency room and ward) due to complications arising from diabetes, COPD, and ischemic cardiopathy (yes/no), and psychiatric pathology (yes/no); mental health referrals (yes/no) and number; and consultations with the family doctor/nurse (yes/no) and number.5.*Variables resulting from the intervention with respect to its feasibility.* A questionnaire with 10 items and a Likert scale of 4 categories regarding satisfaction is administered to the patients on completing the intervention. Adherence is assessed through the number of sessions each IG patient attends. An adherence variable is calculated for the intervention: ≥75% attendance or less.

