Confounding variables and effect modifiers*Pharmacological treatment.* The defined daily dose for each active ingredient is established during the follow-up period taking into account the number of days, the dosage, and the route of administration. The registered active ingredients belong to the following groups: antidepressants, anxiolytics, antidiabetics (oral, insulin), bronchodilators (selective agonists of Beta2 - adrenergic, anticholinergic), anti-inflammatories: corticosteroids, antihypertensives, and dyslipidemics.*Other associated comorbidities:* cardiac insufficiency, atrial fibrillation, cardiovascular disease, peripheral vascular disease, other chronic diseases.Participation in *other mental health therapies* given by psychologists and psychiatrists.*Anxiety* evaluated with the HARS-Hamilton Anxiety Rating Scale [42].*History of previous depressive episodes* (yes/no).

Cost variables

Expenses included in the cost-effectiveness analysis:*Use of primary care services*: consultation fees according to professional status and level of care.*Use of hospital services*: hospitalization and emergency room consultations.*Cost of psychotropic medication consumed during the study*: anxiolytics and antidepressants according to the current catalogue from the Pharmacist Association.*Derived costs*: training and supervision of the nurses responsible for leading the sessions, their working hours spent with the groups, and expenses related to material used in the sessions and given out to the participants. In order to calculate the cost of the resources 2016 Oblikue rates are employed [43].

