### Statistical analysis

The analysis is performed on an intention-to-treat basis. All the patients who have signed the informed consent and attended the initial interview are included. Missing data from the BDI-II evaluation during follow-up will be substituted by the last registered value (Last Observation Carried Forward strategy). At the beginning of the study descriptive statistics will be performed to evaluate the homogeneity between the two groups (IG and CG) with respect to demographic, clinical, and service utilization variables. In order to measure the main objective (rate of remission and response) logistic regression is employed in which the dependent variable is dichotomous (rate of remission and response). The patient’s group is the independent variable. Raw and adjusted odds ratio (OR) are calculated according to age, sex, pharmacologic treatment, and comorbidity. Repeated measure ANOVA analysis will be performed to determine the evolution of the dependent variables during follow-up. For the secondary resulting variables, control of the physical pathologies will be measured by logistic regression in which the dependent variable is dichotomous (control yes/no). The models will be adjusted in the same way as the principal one. Variable differences in the BDI-II rating and other scores with respect to baseline will be calculated. Student’s t test will be employed for the comparison between the groups’ variables and standardized effect size (SES; Kazis et al.1989) [44].

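### The adjusted odds ratio may be biased for the intention-to-treat effect, in either direction, because its drug-treatment covariate is defined by use during follow-up

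*Protocol article*

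**What the plan says.** All places are in the protocol article.

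- **Statistical analysis.** The analysis is by intention to treat. Remission and response are analysed by logistic regression on group: "Raw and adjusted odds ratio (OR) are calculated according to age, sex, pharmacologic treatment, and comorbidity". For control of the physical diseases, "The models will be adjusted in the same way as the principal one". Neither the raw nor the adjusted odds ratio is named as the primary estimate.
- **Measures, confounding variables and effect modifiers.** Pharmacological treatment heads this list. "The defined daily dose for each active ingredient is established during the follow-up period", from days, dosage and route. The drug groups include antidepressants, anxiolytics, antidiabetics, bronchodilators, antihypertensives and drugs for dyslipidaemia.
- **Sample.** Patients already on antidepressants or anxiolytics may enter, and their data are to serve as covariables. No time point is given.
- **Table 3.** Pharmacotherapy is recorded at baseline, 3 months and 12 months; other comorbidities at baseline and 12 months.
- **Description of the psychoeducation group intervention.** The programme covers "health education regarding: diet, physical exercise, sleep, pleasant activities, social skills, pharmacological treatment, and adherence to treatment". Session 6 in Table 1 includes therapeutic compliance.
- **Description of the control group.** "for both groups the healthcare professionals use their own criteria (usual clinical practice) regarding the chronic pathology and depressive symptoms".

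**The concern.** In a randomised comparison, a variable measured after allocation cannot confound the effect of allocation. Adjusting for one can do harm in two ways.

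First, if the programme works partly through better use of medication, holding drug use fixed removes that part of its effect. The authors do expect an effect of this kind: in the Background they say of psychoeducation that "it decreases depressive symptoms and risk of relapse/recurrence, and improves treatment compliance", and adherence to medication is a secondary outcome.

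Second, drug use can reflect how ill the patient is or how the depression is going, since prescribing is left to clinicians in both arms. If allocation also affects drug use, patients compared at the same level of use are no longer alike in severity, and an association can appear or disappear without any effect of the programme.

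The physical-disease models are more exposed. Antidiabetic, respiratory, antihypertensive and lipid drugs taken during follow-up are direct intermediates for HbA1c, lung function, blood pressure and LDL cholesterol.

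At stake is whether the adjusted odds ratio answers the intention-to-treat question that the section announces.

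**Working it through.** **1. Which value enters the model?** Statistical analysis names the covariate without a time. Measures, the only place that defines it, puts it in follow-up. Sample points to treatment at entry but defines nothing. Followed as written, the covariate is the follow-up dose.

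**2. The plan's own figures** (Sample size: 40% v 26%, alpha 5%, power 80%, 189 per group, 252 after 25% dropout). Two-sided, without continuity correction:

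n = [1.96·√(2·0.33·0.67) + 0.8416·√(0.40·0.60 + 0.26·0.74)]² / 0.14² = 175.9.

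With continuity correction: (175.9/4)·[1 + √(1 + 4/(175.9·0.14))]² = 189.9, which is 190 rounded up, against the stated 189. Then 189/0.75 = 252. The calculation contains no covariates, so it is not touched by this point. The planned effect as an odds ratio is (0.40/0.60)/(0.26/0.74) = 1.90.

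**3. Illustration of the mediator path.** Assumptions, none from the documents: drug use is yes/no, 50% in control and m in intervention, and it multiplies the odds of remission by g. Marginal remission stays at 26% and 40%. Let x be the odds of remission without the drug in one arm, and q the share of users in that arm. Then x solves

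(1−q)·x/(1+x) + q·g·x/(1+g·x) = remission rate,

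and the adjusted odds ratio is x(intervention)/x(control).

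For g = 2 and q = 0.5 in control: 2.96x² + 1.44x − 0.52 = 0, so x = 0.2414. For m = 0.7: 1.2x² + 0.5x − 0.4 = 0, so x = 0.4055. The ratio is 1.68.

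| m | g | x control | x intervention | Adjusted OR | Simulated power, 189 per arm |
|---|---|---|---|---|---|
| 50% | 2 | 0.2414 | 0.4657 | 1.93 | 0.83 |
| 60% | 2 | 0.2414 | 0.4343 | 1.80 | 0.72 |
| 70% | 2 | 0.2414 | 0.4055 | 1.68 | 0.63 |
| 70% | 3 | 0.1886 | 0.2989 | 1.59 | 0.51 |

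Power comes from simulation with 400,000 patients per scenario; for the raw odds ratio it was 0.80 to 0.82. The simulated adjusted odds ratios were 1.92, 1.77, 1.68 and 1.59; the 1.77 goes with a raw value of 1.87 in that sample. In the first row drug use is equal in both arms and there is no bias: 1.93 exceeds 1.90 only because odds ratios are non-collapsible, and the standardised risk difference stays at 14 points. In the third row it falls to 11 points.

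**4. Illustration with severity.** Same simulation, with a standard normal severity variable, not in the model, that adds 0.8 to the log odds of drug use and subtracts 0.8 from the log odds of remission. The raw odds ratio was 1.89 to 1.90.

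| Drug use, control to intervention | Drug–remission OR | Adjusted OR | Standardised risk difference, adjusted v raw |
|---|---|---|---|
| 50% to 35% | 0.5 | 1.67 | 10.5 v 14.0 points |
| 50% to 35% | 1.5 | 1.85 | 13.5 v 13.9 points |
| 50% to 65% | 1.5 | 1.94 | 14.5 v 14.0 points |

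**5. No true effect.** Again under assumption, with sicker patients using more drugs and control use at 50%: the raw odds ratio is about 1.0, and the adjusted one is 1.10 to 1.14 if intervention use is 63–66%, and about 0.92 if it is 37%. These values need a strong link between severity and drug use; with a weaker link they lie closer to 1.

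**The case against.** The case on the other side is substantial.

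- **The raw odds ratio is planned too.** This stands. It contains no post-randomisation covariate and estimates the effect of offering the programme. A reader might infer that the trial's treatment effect is biased outright; the text does not support that. What remains is that either estimate could become the headline.
- **The covariate may be baseline treatment.** The Sample section allows this reading, and covariate timing is often left to an analysis plan. But the article does state a definition, and it says follow-up, so the places must be reconciled.
- **Dose is not adherence.** Adherence is measured separately, by questionnaire and by containers collected ("It will be performed for all the prescribed medication for both groups"), and prescribing is the clinicians' choice. So an effect of the programme on the defined daily dose is plausible, not shown. This stands, and it makes the bias conditional.
- **The sizes are assumed.** This stands. Only 40% v 26% comes from the document.

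A reader might also extend the point to comorbidity at 12 months, follow-up anxiety scores and concurrent mental health therapies. The documents do not support that. Table 3 lists other comorbidities under cost variables, and nothing says the 12-month value enters an effectiveness model. Anxiety and other therapies are in the list of confounders but not in the adjustment set under Statistical analysis.

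**Conclusion.** The concern holds in conditional form. As the article defines it, the drug covariate is measured after randomisation, on a pathway that the programme addresses and that clinicians may alter. The adjusted odds ratio therefore need not estimate the intention-to-treat effect, in the primary model or in the physical-disease models. Bias arises only if drug use is affected by allocation or by the course of depression.

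Its size and direction cannot be derived from the documents. Against a planned odds ratio of 1.90, the illustrations with drug use differing by arm gave 1.59 to 1.94, mostly towards no effect but not always, so the adjusted estimate cannot be defended as conservative. The raw odds ratio and the sample size are sound on this point.

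**What to change.** In Statistical analysis, state that the primary and physical-disease models are adjusted only for pharmacotherapy recorded at baseline, and that comorbidity is the baseline value. Bring the definition under Measures and the remark in Sample into line with this. Name which odds ratio, raw or baseline-adjusted, is the primary estimate. Report follow-up drug use by arm descriptively, or use it in an analysis labelled exploratory.

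The cost is a few sentences. Table 3 already collects both baseline variables, no new data are needed, and 189 and 252 per group stand.

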### Sample size

A power analysis will be conducted to determine the appropriate sample size. A previous study of psychoeducation programs [18] reported a remission rate at 9 months follow-up of 40% in the IG and 26% in the CG. Assuming a 5 and 20% alpha and beta risk, respectively, 189 patients are required for each group. Due to a number of reasons, an approximately 25% dropout rate is expected, consequently, 252 participants per group need to be recruited (total *n* = 504). In addition, 25 PHC are required each with a mean of 20 patients (IG *n* = 10, CG *n* = 10).

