### Measures

The selected variables and instruments, as well as the evaluation program timeline, are detailed in Table 3. Data will be imported using an online survey tool and include:

**Table 3 Tab3:** Outcome measures

Outcome measures	Timeline		
	Pre-intervention	Post-intervention	
		3 mo	12 mo
1. Socio-demographic variables			
Sex, age, marital status, educational level, employment status, reference PHC	X		
2. Diagnostic variables			
Diagnosis depression: MINI	X		
Diagnosis chronic physical illness: ICD-10	X		
Suicide risk: MINI	X		
Cognitive impairment: Pfeiffer questionnaire	X		
3. Clinical variables			
Depressive symptoms: BDI- II questionnaire	X	X	X
Anxiety symptoms: HARS questionnaire	X	X	X
Quality of life: EQ-5D-5 L questionnaire	X	X	X
Pharmacotherapy	X	X	X
Therapeutic compliance: Morinsky-Green test	X	X	X
Feasibility of the intervention	X	X	
4. Blood test and Physical parameters			
Type 2 diabetes mellitus: Analytical HBA1C	X		X
COPD: FEV1 and Medical Research Coincil (mMRC)	X		X
Asthma: Spirometry and Peak flow	X		X
Ischemic heart disease: Analytical cholesterol LDL and Blood pressure	X		X
5. Costs variables			
Pharmacological Treatment	X	X	X
Utilization of services: PHC and hospital	X	X	X
Other comorbidities	X		X
Costs derived from the intervention	X	X	X

*Abbreviations*: *mo* months, *BDI-II* Beck Depression Inventory secondary edition, *COPD* Chronic obstructive pulmonary disease, *EQ* EuroQuol, *FEV1* Forced expiratory volume, *HARS* Hamilton Anxiety Rating Scale, *HBA1C* Hemoglobin A1C test, *ICS-10* International classification of diseases-10th revision, *MINI* Mini international neuropsychiatric interview, *PHC* Primary Healthcare Centers

Diagnostic variables*Diagnosis of depression* according to the MINI interview [27, 28].*Physical diseases* (code CIE-10). Diagnosis of diabetes mellitus (E11-E14 and sub-groups), COPD (J43-J44 and sub-groups), asthma (J45), and/or ischemic cardiopathy (I20-I25 and sub-groups) as registered in the patients’ medical records and confirmed by their family doctor [29].*Risk of suicide* evaluated by the MINI interview [27, 28].*Pfeiffer Scale* to detect cognitive impairment [30, 31]. This is a hetero-administered questionnaire made up of 10 items and scored from 0 to 10 (errors). From 5 onwards an individual is considered to present moderate/severe cognitive decline.

Socio-demographic variables:

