Some limitations include the fact that the nurses who carry out the intervention are aware of the groups the patients belong to. Nevertheless, blinding of some key stages of the study, such as randomization, evaluation of outcomes/confounder variables, and statistical analysis will be maintained. Second, for a long-term follow-up under normal conditions a dropout rate of 25% is expected. In the case of missed appointments and intervention sessions it is hoped that patient adherence will be ensured through telephone calls (at least three times per appointment, one of which is 24 h prior to the appointment) unless the patient has stated reluctance to participate. Third, the patients will present varying pathologies which will increase the heterogeneity of the sample. Nevertheless, most of the patients attended at the PHC present comorbidities and their inclusion represents a greater generalization of results. Fourth, in order to avoid the effect of contamination, patients assigned to the two nurses leading the IG from the same center will be excluded. Fifth, there could be some difficulty in recruiting a sufficient number of patients.

To the best of our knowledge, this is the first study evaluating the effectiveness of a psychoeducation group intervention with patients suffering from both depression and a chronic organic pathology (diabetes mellitus, COPD, asthma, and ischemic cardiopathy) to be carried out by community nurses in a primary care setting.

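### The adjusted primary odds ratio leaves out baseline anxiety and previous depressive episodes, which the protocol itself names as confounders or effect modifiers

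*Protocol article*

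**What the plan says.** The Measures section has a list of confounding variables and effect modifiers with five entries: drug treatment, other associated comorbidities, participation in "other mental health therapies", anxiety by HARS, and "History of previous depressive episodes" (yes/no).

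The Statistical analysis section sets the primary model as a logistic regression with trial arm as the independent variable, and then says: "Raw and adjusted odds ratio (OR) are calculated according to age, sex, pharmacologic treatment, and comorbidity". The models for control of the physical diseases are to be adjusted in the same way.

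On timing, the Measures section says "The selected variables and instruments, as well as the evaluation program timeline, are detailed in Table 3". Table 3 has HARS at baseline, 3 and 12 months. It has no row for previous episodes or for participation in other therapies.

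The Discussion, under limitations, adds that "the patients will present varying pathologies which will increase the heterogeneity of the sample".

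**The concern.** The article names its confounders in one section and adjusts for only some of them in the next. Of the five listed factors, only drug treatment and comorbidity reach the model. Two of the three left out, anxiety and previous episodes, describe the patient before randomisation. They are therefore legitimate covariates for a remission or response outcome, and the authors evidently regard them as prognostic.

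Three things are at stake, none of them large:

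- Some power is given up if the two factors do predict remission.
- A chance imbalance in either would not be corrected in the adjusted estimate.
- With the list and the model out of step, someone could later argue for either covariate set once results are known.

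**Working it through.** **1. The plan's own figure.** The Sample size section takes remission of 40% (intervention) and 26% (control) from an earlier psychoeducation study. Its error rates and result are: "Assuming a 5 and 20% alpha and beta risk, respectively, 189 patients are required for each group". A 25% allowance for dropout then brings recruitment to 252 per arm. Sidedness is not stated, so two-sided is assumed.

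Pooled two-proportion formula, with p̄ = (0.40 + 0.26)/2 = 0.33:

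n = [1.960·√(2·0.33·0.67) + 0.842·√(0.40·0.60 + 0.26·0.74)]² / 0.14² = 175.9, i.e. 176

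With continuity correction: n' = (n/4)·[1 + √(1 + 4/(n·0.14))]² = 189.9, i.e. 190

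The stated 189 agrees with the corrected formula to within one patient, and 189/0.75 = 252 exactly. No covariate enters this calculation, so the sample size does not depend on the present point.

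**2. List against model.**

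| Listed confounder or modifier | In adjusted model? | Fixed before randomisation? |
|---|---|---|
| Drug treatment | yes | defined over follow-up |
| Other comorbidities | yes, as comorbidity | yes, at its baseline assessment |
| Other mental-health therapies | no | no, if received during follow-up |
| Anxiety (HARS) | no | yes, at its baseline assessment |
| Previous depressive episodes | no | yes, by nature |

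Only the last two rows are baseline factors that are both named and unused.

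**3. What adjustment would gain.** The article gives no prognostic strength for either factor, so a range was assumed. Setting: 189 per arm, marginal remission held at 26% and 40%, 4,000 simulated trials per scenario, Wald test at 5% two-sided, and one standard-normal baseline score standing in for the two factors together.

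| Assumed OR per SD | Power without | Power with | Gain (points) |
|---|---|---|---|
| 1.00 | 82.1% | 82.2% | 0.1 |
| 1.35 | 81.8% | 82.8% | 1.0 |
| 1.65 | 81.8% | 83.3% | 1.5 |
| 2.23 | 83.5% | 87.4% | 3.9 |
| 2.72 | 82.7% | 87.9% | 5.2 |

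The variation in the middle column is simulation noise (standard error about √(0.82·0.18/4000) = 0.6 points).

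A second simulation entered the two factors separately, assuming that 60% of patients have a previous episode. It gave the same picture:

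- History OR 0.7 and HARS OR 0.8 per SD: about 83% to 84%.
- 0.5 and 0.65: about 82% to 84%.
- 0.4 and 0.5: about 82% to 87%.

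**4. Where the gain comes from.** In the first simulation the standard error of the log odds ratio does not fall with adjustment. It goes from 0.224 to between 0.224 and 0.247. The log odds ratio itself moves away from zero, from about 0.64–0.65 to between 0.65 and 0.77. The benefit is power, not a narrower interval on the log-odds scale.

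**5. Chance imbalance.** With 60% prevalence (assumed), the standard error of the between-arm difference is √(2·0.6·0.4/n).

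- n = 252: 0.0436; 0.08/0.0436 = 1.83, so a difference of at least 8 points in either direction arises in about 7% of trials.
- n = 189: 0.0504; 0.08/0.0504 = 1.59, about 11%.

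**The case against.** The strongest reply is that a shorter prespecified adjustment set is a legitimate choice. Allocation is randomised and a raw odds ratio is reported, so omitting baseline covariates does not bias that comparison. A list of confounders and effect modifiers does not promise that each item becomes a main effect, and the gain is small. All of this stands, and it limits the weight of the point. It does not explain why two factors that the authors name, one of them already scheduled at baseline, are left out of a model that adjusts for other factors from the same list.

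Four stronger readings are tempting and are not supported:

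- *That co-treatment goes unmeasured.* Participation in other therapies is a listed study variable. Mental-health referrals and psychiatric admissions are secondary-outcome items, and Table 3 schedules pharmacotherapy and service use at all three times. Referrals are only a proxy, since they do not show attendance and may miss privately arranged therapy. The missing Table 3 rows are still a minor scheduling gap in a condensed article; the pharmacy-container comparison has no row of its own either.
- *That other therapies belong in the model.* Those received after randomisation may be affected by allocation, and adjusting for them could bias the treatment effect. Leaving them out is right. The same caution bears on the drug-treatment covariate, which the Measures section defines over follow-up, but that is a separate matter.
- *That the qualifying disease is omitted.* The analysis section says only comorbidity. The Background uses that word for the physical illness accompanying depression, while the Measures list refers to other, additional conditions. The term is ambiguous, so an omission is not shown.
- *That precision is lost at no cost.* Step 4 shows that the standard error does not shrink.

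**Conclusion.** The point holds in a limited form: the adjusted primary model omits two baseline factors that the protocol itself names. The loss is about 0 to 5 percentage points of power at 189 per arm, plus uncorrected chance imbalance in those factors.

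The size rests on assumed prognostic strengths, an assumed 60% prevalence of previous episodes, and covariates unrelated to those already in the model. Overlap with the existing covariates would reduce the gain. So would analysing all 252 per arm, where unadjusted power at the same rates is already about 92%. The upper end of the range needs strong effects (an OR of 2.7 per SD for a combined score, or 0.4 for history with 0.5 per SD for anxiety).

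Neither the stated sample size nor the validity of the raw odds ratio is in question. This is a worthwhile improvement, not a flaw that threatens the trial's conclusion.

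**What to change.** In the Statistical analysis section:

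1. Add baseline HARS (continuous) and previous depressive episodes (yes/no) to the prespecified adjusted logistic model. Use only the baseline HARS value, because the 3- and 12-month values are post-randomisation.
2. State that comorbidity includes the qualifying disease (diabetes, COPD, asthma, ischemic cardiopathy).
3. State that other mental-health therapies received after randomisation are not covariates and will be reported by arm.

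As tidying, give a collection time in Table 3 for previous episodes (baseline) and for therapy participation (follow-up).

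The cost is a sentence or two of text and a few more model parameters, which 504 patients can carry. HARS is already scheduled at baseline and the other two items are already listed as study variables, so no new instrument is needed.
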